## Number of Subjects, Number of Study Arms & Number of Study Cohorts

The study will randomize 135 subjects, irrespective of gender, who fulfill all enrollment criteria. These subjects will be recruited into one of 3 cohorts (dosage groups), each containing a total of 45 subjects. Each cohort will be composed of 15 subjects in each of 3 age groups (12-23 months, 24-35 months, and 36-47 months; monthly ages are rounded down, e.g., a child who is 24.5 months old is considered to be 24 months old). Moreover, each cohort will be composed of 30 FMP-1 recipients (either 10 g, 25 g or 50 g) and 15 Imovax® (comparator vaccine) recipients.

Age-stratification will be maintained down to the smallest groups; i.e., an FMP-1 to Imovax® ratio of 10: 5 will be maintained in each age-group of a given cohort. Recruitment of subjects into each age-group of a cohort will be separately incremental (i.e., recruitment will not stop in any age group of a cohort until 15 children have been recruited, randomized, and vaccinated). Recruitment will stop altogether when the total number of subjects enrolled has reached 135.

Cohort A: The 30 subjects receiving 1/5th dose = 10 g of FMP-1 (10 subjects from each of the 3 age groups), plus the 15 subjects receiving the Imovax® comparator (5 subjects from each of the 3 age groups), together constitute Cohort A.

Cohort B: The 30 subjects receiving ½ dose = 25 g of FMP-1 (10 subjects from each of the 3 age groups), plus the 15 subjects receiving the Imovax® comparator (5 subjects from each of the 3 age groups), together constitute Cohort B.

Cohort C: The 30 subjects receiving full dose = 50 g of FMP-1 (10 subjects from each of the 3 age groups), plus the 15 subjects receiving the Imovax® comparator (5 subjects from each of the 3 age groups), together constitute Cohort C.

These age groups, study arms and cohorts are presented in tabular fashion in Tables 2 and 3.

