### **7.9.2 Criteria for Discontinuation of Vaccination**

If any of the following SAEs occur, discontinuation of vaccination will be invoked and the events will be reported as described in Section 11.5.

1. Death in any subject in which the cause of death is judged to be possibly, probably or definitely related to study vaccine
2. The occurrence in any subject of an anaphylactic reaction to study vaccine
3. The occurrence in any subject of a life-threatening SAE whose causal relationship to vaccination is judged to be probable or definite
4. The occurrence of one or more non-life-threatening SAEs whose causal relationship to vaccination is judged to be definite
5. The occurrence, in one or more subjects, of Grade 4 laboratory abnormalities (See Table 5, “General Toxicity Table”), judged to be probably or definitely related to receipt of study vaccine

The following dose limiting toxicities will preclude dose escalation to the next higher dose level or administration of consecutive doses within a dose level (See Table 5):

1. In 4 (10%) or more children within a cohort, occurrence of Grade 3 or greater solicited systemic (not local) AEs judged probably or definitely related to the study vaccine, , , or
2. In 4 (10%) or more children within a cohort, occurrence of Grade 2 or greater unsolicited AEs judged probably or definitely related to the study vaccine, or
3. In 4 (10%) or more children within a cohort, occurrence of laboratory studies indicating Grade 2 or greater toxicities that are judged to be probably or definitely related to the study vaccine.

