### **7.9.6 Dose Discontinuation in Individual Subjects**

Reasons for discontinuation of study vaccine administration in an individual subject include, but are not limited to, the following:

1. Anaphylactic reaction following administration of study vaccine
2. Significant (Grade 3 or 4) reactions following administration of study vaccine (including severe pain, severe swelling, severe headache, persistent high fever or other severe systemic or local reactions) that, in the opinion of the investigator or sponsor, preclude further administration of study vaccine
3. The occurrence of an SAE (See Section 11.5.1) whose relationship to the study vaccine is judged to be possible or probable
4. Receipt of any investigative drug, investigative vaccine or immunosuppressive medication (inhaled or topical corticosteroids are allowed) within 28 days of study vaccine
5. The occurrence of other medical conditions, unrelated to study vaccine, which, in the opinion of the PI, contraindicate administration of study vaccine
6. Moderate or severe unsolicited AEs (clinical events or laboratory tests) that are indicative of new and significant end organ dysfunction

**Table 5: General Toxicity Table** (Modified from the Pediatric ACTG Toxicity Tables; See Ref. 43)

| **Event** | **Grade I** | | **Grade 2** | | **Grade 3** | | | **Grade 4** | |
| --- | --- | --- | --- | --- | --- | --- | --- | --- | --- |
| **Laboratory Values** | | | | | | | | | |
|  | Conventional  Units | SI Units | Conventional Units | SI Units | Conventional Units | SI Units | | Conventional Units | SI Units |
| Hemoglobin | 7.0-7.9 gm/dL | 4.4-4.9 mmol/L | 6.0-6.9 gm/dL | 3.8-4.39 mmol/L | <6.0 gm/dL | <3.8 mmol/L | | CHF 2o to anemia | CHF 2o to anemia |
| Leukocytes | 3.0-3.9 103  per mm3 | 3.0-3.9 109/L | 2.0-2.9 103  per mm3 | 2.9-2.0 109/L | 1.0-1.9 103  per mm3 | 1.9-1.0 109/L | | <1.0 103  per mm3 | <1.0 109/L |
| Platelets | 90,000-109,999 per mm3 | 90.0-109.9 109/L | 75,000-89,999  per mm3 | 75.0-89.9 109/L | 50,000-74,999 per mm3 | 50.0-74.9 109/L | | <50,000 per mm3 | <50.0 109/L |
| Creatinine | 1.1-1.9 mg/dL | 92-176 mol/L | 2.0-3.9 mg/dL | 177-353 mol/L | 4.0-5.9 mg/dL | 354-530 mol/L | | >6.0 mg/dL | >530 mol/L |
| ALT | 45-60 IU/l | 45-60 IU/l | 61-105 IU/l | 61-105 IU/l | 106-147 IU/l | 106-147 IU/l | | > 148 IU/l | > 148 IU/l |
| **Systemic Events** | | | | | | | | | |
| Fever | 37.5-38.0oC | | 38.1-39.0oC | | 39.1-40.5oC | | >40.5o persistent >48 hours | | |

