## Eliciting & Documenting Adverse Events

### **Definition of an Adverse Event**

Serious adverse events (SAEs) are discussed in Section 11.5 below.

An adverse event (AE) includes any noxious, pathological or unintended change in anatomical, physiological or metabolic functions as indicated by physical signs, symptoms or laboratory test abnormalities occurring in any phase of the clinical study whether associated with the study vaccine and whether or not considered vaccine-related. This includes an exacerbation of pre-existing conditions or events, intercurrent illnesses, or vaccine or drug interaction or the significant worsening of the disease under investigat-ion that is not recorded elsewhere in the CRF. A symptom present just prior to a first vaccination, and not exacerbated after the vaccination is administered, should not be considered an AE. Similarly, anticipated day-to-day fluctuations of pre-existing conditions,including the disease under study, that do not represent a clinically significant exacerbations need not be considered AEs. However, discrete episodes of chronic conditions occurring during a study period (after the first vaccination) should be reported as AEs in order to assess changes in frequency or severity.

AEs should be documented in terms of a medical diagnosis. When this is not possible, an AE will be documented in terms of signs and symptoms observed by the investigator or reported by the subject at each study visit.

Pre-existing conditions, or signs and symptoms (including any which are not recognized at study entry but are recognized during the study period), which are present in a subject prior to the start of the study should be recorded on the Medical History Form within the subject's CRF. Any of the signs or symptoms to be solicited present during physical examination of the subject at each vaccination visit should be recorded on the Pre-Vaccination Assessment page of the subject's source document.

AEs which occur after informed consent is obtained, but prior to a first vaccination, will be documented on the Medical History Form within the subject's CRF.

Any non-elective hospitalization will be considered an SAE, rather than an AE, regardless of the reason for hospitalization and possible causal relationship to vaccine administration (See Section 11.5).

Solicited AEs to be recorded are described in Section 11.1.5 . Any other AEs will be recorded as unsolicited AEs.

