## Assessment of Causality

Every effort will be made by the investigator to explain each AE and determine its causal relationship, if any, to administration of the study vaccine.

The degree of certainty with which an AE can be attributed to administration of the study vaccine (or alternative causes, e.g., natural history of underlying diseases, concurrent therapy, etc.) will be determined by how well the event can be understood in terms of one or more of the following:

- Reactions of a similar nature having previously been observed with this type of vaccine or formulation.
- The event having often been reported in literature for similar types of vaccines.
- The event being temporally associated with vaccination or reproduced on re-vaccination.

All solicited local (injection site) reactions will be considered causally related to vaccination.

Assessment of causality in all other AEs should be documented by the investigator by answering the following query on the “Serious and Unexpected Adverse Event Report”:

In your opinion, did the vaccine(s) possibly contribute to the adverse event?

NO; Either the adverse event is not causally related to administration of the study vaccine or

there are other, more likely causes and administration of the study vaccine is not suspected

to have contributed to the adverse event.

YES; There is a reasonable possibility that the vaccine contributed to the adverse event.

Non-serious and serious AEs will be evaluated as two distinct events given their different medical nature. If an event meets the criteria to be determined “serious” (see Section 11.5.1 for definition of an SAE), it will be investigated by the PI to the extent that a determination of ALL relevant contributing factors can be made.

A partial list of possible contributing factors might include:

- Past medical history
- Concurrent medications
- Protocol required procedures
- Lack of efficacy of the test vaccine
- Erroneous vaccine administration

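### The protocol supports two readings of whether a hospitalised child counts as an adverse event, which give different dose-limiting counts, and its hold and restart rules for a probably related non-life-threatening SAE do not agree

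*Protocol*

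**What the plan says.** **Classification.** Section 11.1.1 states: "Any non-elective hospitalization will be considered an SAE, rather than an AE, regardless of the reason for hospitalization". Events outside the solicited list are then recorded as unsolicited AEs. Section 11.3 adds: "Non-serious and serious AEs will be evaluated as two distinct events given their different medical nature". Section 11.1.3 puts AEs on the Adverse Event Form and refers SAEs to 11.5, where 11.5.2 gives them a separate form.

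**Stopping items in 7.9.2.** The first list names single events that discontinue vaccination: a related death (item 1), anaphylaxis (item 2) and a related Grade 4 laboratory abnormality (item 5), together with:
- item 3: "The occurrence in any subject of a life-threatening SAE whose causal relationship to vaccination is judged to be probable or definite"
- item 4: "The occurrence of one or more non-life-threatening SAEs whose causal relationship to vaccination is judged to be definite"

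**Dose-limiting limbs in 7.9.2.** Escalation and the next dose are barred when four or more children in a cohort are affected. Limb 1 counts "occurrence of Grade 3 or greater solicited systemic (not local) AEs judged probably or definitely related to the study vaccine". Limb 2 counts "occurrence of Grade 2 or greater unsolicited AEs judged probably or definitely related to the study vaccine". Limb 3 counts Grade 2 or greater laboratory toxicities at the same causality levels. The cohorts are described as "each containing a total of 45 subjects", made up of 30 FMP-1 and 15 rabies vaccine recipients.

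**Child level.** Section 7.9.6 item 3 gives, as a reason to stop dosing a child, an SAE "whose relationship to the study vaccine is judged to be possible or probable".

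**Hold outside 7.9.2.** Under 11.5.2, any SAE suspected of being related stops vaccination in all subjects until a written report has gone to the listed bodies and the investigators have conferred with the Local Medical Monitor (LMM).

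**Analysis.** Section 13.5.3 tabulates children with local, general and unsolicited AEs. It describes SAEs and compares their incidence separately.

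**The concern.** The safety endpoints and limbs 1 and 2 are worded in AEs. If an admission is not an AE, the most severely affected children are absent from the counts meant to detect them. A vaccine that turned non-serious reactions into admissions would then show a lower AE incidence and come less close to the four-child limit.

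The second issue is the rule for one event. A non-life-threatening SAE judged probable falls between items 3 and 4 of 7.9.2, yet 11.5.2 stops the whole trial for it. The site needs to know which procedure it is in, because the two end in different ways.

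**Working it through.** **1. The plan's own figure.** The limit is given as 4 children (10%). Ten percent of 45 is 0.10 × 45 = 4.5. Four children are 4/45 = 8.9% of a cohort, or 4/30 = 13.3% of its FMP-1 recipients. The percentage is approximate, and the operative number is 4.

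**2. Is an admitted child an AE?**
- *Pointing to no:* the contrast in 11.1.1; the separate form in 11.5.2; the separate listing of AEs and SAEs in 7.9.3; their separate analysis in 13.1 and 13.5.3.
- *Pointing to yes:* 11.3 speaks of serious AEs. Section 11.5.1 says that an untoward occurrence during an elective procedure is an AE of either the serious or the non-serious kind. Limb 1 covers Grade 3 or greater, and Table 5 defines Grade 4 drowsiness and irritability by seizures or coma, which would ordinarily be serious.
- *Not decisive:* 11.1.2 records all AEs whatever their severity, but only once the event is an AE, and severity is not seriousness.

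**3. Effect on the dose-limiting count.** Take three children with non-serious Grade 2 unsolicited events and one admitted with an event that would otherwise qualify, all probable. If serious events are AEs, limb 2 counts 3 + 1 = 4 and the limit is reached. On the literal reading it counts 3 and the limit is not reached.

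**4. Effect on the tables.** One admitted child with no other AE changes the percentage by 1/30 = 3.3 points in a 30-child arm, or 1/15 = 6.7 points in a 15-child arm.

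**5. Illustration of the limit.** The protocol gives no event rates, so both inputs are assumptions: p is the share of 30 FMP-1 recipients with a qualifying related event, and h is the share of those who are admitted. With independent children, the number counted on the literal reading is binomial with n = 30 and probability p(1 − h). The chance of reaching 4 is:

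| p | all counted | h = 10% | h = 25% | h = 50% |
|---|---|---|---|---|
| 5% | 0.061 | 0.044 | 0.025 | 0.006 |
| 10% | 0.353 | 0.283 | 0.184 | 0.061 |
| 15% | 0.678 | 0.591 | 0.441 | 0.184 |
| 20% | 0.877 | 0.814 | 0.678 | 0.353 |
| 25% | 0.963 | 0.930 | 0.840 | 0.527 |

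**6. One probably related, non-life-threatening SAE against 7.9.2.** Item 1 (death): no. Item 2 (anaphylaxis): no. Item 3 (life-threatening): no. Item 4 (definite): no. Item 5: no, unless it is a Grade 4 laboratory abnormality. Limbs 1 and 2: at most 1 of the 4 needed, and 0 on the literal reading. No 7.9.2 rule acts on the single event under either reading.

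**7. The same event elsewhere.** If suspected of being related, it triggers the 11.5.2 hold. Section 7.9.1 defines discontinuation as temporary or permanent withholding of further vaccination, so the hold fits that definition. The exits differ: 11.5.2 ends on a written report and conferring with the LMM, while 7.9.5 requires a meeting and a unanimous decision to restart. Condition 4 for escalation (7.9.3) and for the next dose (7.9.4) tests only for 7.9.2 events, so this event does not fail it.

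**8. Causality scale.** For AEs other than solicited local reactions, 11.3 records causality as NO or YES. Sections 7.9.2 and 7.9.6 need possible, probable and definite, which that assessment does not produce.

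**The case against.** The strongest reply is that 11.1.1 only classifies seriousness and points to 11.5. No passage says that SAEs are removed from AE tables or dose-limiting counts, and several treat them as AEs. That stands: a reader might infer a stated exclusion, and the protocol does not contain one. What it contains is wording that supports both readings.

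A reader might also infer that any number of probably related admissions would leave escalation unimpeded. The documents do not support that. One suspected related SAE halts all vaccination under 11.5.2. The LMM reviews SAEs and must recommend each escalation and each consecutive dose, and the Data and Safety Monitoring Board (DSMB) must concur before doses 1b and 1c. The LMM may suspend the trial in exceptional circumstances, and the DSMB may put it on hold. These safeguards limit the consequence, but they do not settle what counts towards four or which restart procedure applies.

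Three narrower replies also stand. Limb 3 counts laboratory toxicities, so an admitted child with a qualifying value is counted under either reading. Grade 1 events never count, so mild events alone cannot reach the limits. Section 7.9.6 omits a definite relationship, but its list is expressly not exhaustive, so that is a drafting mismatch and not a reversed rule.

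Finally, the layout of the tables may be left to an analysis plan that is not shown. That is fair for 13.5.3. It does not answer the count applied between doses, which the protocol itself must fix.

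**Conclusion.** The point holds as two inconsistencies to be reconciled.

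First, the AE wording gives two readings, and the choice can decide whether a cohort reaches the limit: one admitted child is enough to turn 4 into 3. On assumed rates of p = 15% and h = 25%, the chance of reaching the limit is 0.678 with admitted children counted and 0.441 without. At p = 10% and h = 25% it is 0.353 and 0.184. These figures rest on assumed rates and independent children, and they show sensitivity only.

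Second, a probably related, non-life-threatening SAE is outside the single-event items of 7.9.2 but inside the hold of 11.5.2, with a different exit from 7.9.5.

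SAEs are not lost to the trial: they are a component of the primary endpoint, they are compared between groups, and the LMM reviews them. The matter is still worth settling before dosing, because safety is the primary objective and the limits are applied in real time.

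**What to change.** 1. In 11.1.1, replace the contrast between SAE and AE with a statement that a serious event is an AE that is also serious. In 13.5.3, say that one with onset in the 7-day or 30-day window stays in the AE incidence tables and is also listed as an SAE.
2. State in 7.9.2 whether serious events count towards the four-child limits. This must be explicit, because the new definition would otherwise settle it by default.
3. Reconcile 7.9.2, 7.9.5, 7.9.6 item 3, 11.3 and 11.5.2 so that every SAE causality category falls under one stated rule with one stated exit, and align condition 4 of 7.9.3 and 7.9.4 with it. The scale in 11.3 has to yield the categories that the rules use.

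Which stopping or restart rule applies is for the sponsor to decide. The cost is a few sentences and no additional visits or samples. If graded causality is kept, the form must record it.

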### **Surveillance Period for Occurrence of Adverse Events**

All AEs occurring within one month (maximum 30 days) following administrat-ion of each dose of vaccine must be recorded on the Adverse Event Form in the subject's CRF, irrespective of severity or likelihood of vaccination-relatedness.

### **Recording of Adverse Events**

At each visit/assessment, all AEs either observed by the investigator or one of his clinical collaborators or reported by the subject’s parent(s) spontaneously or in response to a direct question will be evaluated by the investigator. AEs not previously documented in the study will be recorded in the Adverse Event Form within the subject's CRF. The nature of each event, date and time (where appropriate) of onset, outcome, intensity and relationship to vaccination will be established. Details of any corrective treatment should be recorded on the appropriate page of the source document. See Section 11.5 for instructions for reporting and recording of SAEs.

As a consistent method of soliciting AEs, the subject’s parent(s) will be asked a non-leading question such as:

"Has the child behaved or reported feeling different in any way since receiving the vaccine or since the previous visit?"

N.B. The investigator should record only those AEs having occurred within the time frames defined above, see Section 8.2.

AEs already documented in the CRF, i.e. at a previous assessment, and designated as ‘ongoing’ should be reviewed at subsequent visits, as necessary. If these have resolved, the documentation in the CRF should be completed. If an AE changes in frequency or intensity during a study period, a new record of the event will be started.

Solicited AEs will be elicited for the first 4 days and on day 7 post-immunization and unsolicited AEs will be recorded during a 30-day follow-up period (day of vaccination and 29 subsequent days). SAE’s will be recorded through the 6th month after the last vaccination (through Study month 8). Thereafter, SAEs are not recorded/reported, although malaria episodes are documented and blood samples are collected for immunological testing.

### **Reporting of Adverse Events**

Reports detailing solicited AEs will be provided by the PI to the DSMB (See Sections 7.9.3 and 7.9.4 for details) after doses 1a and 1b (See also Section 8.1.2: ‘Vaccination Process’ and Appendix B [Section 17.2.5: ‘Specific Schedule of Events’]). These reports will reflect solicited AE data as of Study days 7 and 21, respectively. It is on the basis of its review of these reports that the DSMB renders concurrence or non-concurrence for the dose escalations represented by doses 1b and 1c, respectively. Add-itionally, the DSMB’s concurrence to proceed to dose 1c, would represent concurrence for all subsequent doses (Doses 2a through 3c) as well. Although the DSMB receives 2 more AE/SAE reports (after consecutive doses 2 and 3; see Section 7.9.4), no further directives are required for the subsequent dose escalations.

Reports detailing solicited AEs will be provided by the PI to the LMM 8 days after each of the 9 doses (i.e., provisionally on, Study days 8, 22, 36, 37, 50, 64, 65, 78, and 92) After reviewing each report, the LMM will, if he concurs, recommend proceeding with the next scheduled dose. This concurrence may be given informally (e.g., telephonically) but will be recorded by the PI in the study regulatory file.

### **Solicited Adverse Events**

**Table 12. Solicited Adverse Event (AE) Categories**

| Categories | Adverse Events |
| --- | --- |
| Local (injection site) AEs | Pain at the injection site |
| Swelling at the injection site |
| General (systemic) AEs | Fever (i.e., axillary temperature  37.5°C) |
| Drowsiness |
| Loss of appetite |
| Irritability/fussiness |

N.B.: Axillary temperature will be recorded at the time of the clinic visit. Should additional temperature measurements be recorded at another time of day, the highest temperature will be recorded.

The assessment of severity/intensity will be as described in Section 11.2. For general signs and symptoms reported, the investigator should assign a causality as described in Section 11.3.

For all signs and symptoms reported, the investigator should report the outcome as described in Section 11.4.

**If an SAE (see Section 11.5) occurs at any time during the study period, the PI will inform the USAMRMC-RCQ within 24 hours by e-mail, fax or telephone and with a written report within 3 working days. The WRP/KEMRI Ethics Review Commit-tee, GSK Biologicals, HSRRB, MVI, the DSMB and the Local Medical Monitor will also receive the written report and so will also be notified within 3 working days.**

